## 7. Randomization

Patients will be randomly allocated to case management (PTC) or usual care (TAU) at individual-level in the ratio of 1:1 stratified by

- (i) type of medical treatment (insulin vs. oral medication/no medication) of their index disease (type 2 diabetes) and
- (ii) study center (PCP).

Type of medical treatment has been identified as the strongest predictor of diabetes self-care in the preceding (unpublished) scoping review, and is thus captured by a physician reported questionnaire to serve as validated stratification criteria. We will hence perform stratified block randomization with variable block lengths to ensure study groups of approximately equal size. The block sizes will not be disclosed, to ensure concealment. Instead, this specific information will be provided in a separate document with restricted access only to the randomization authority. The randomization procedure is closely linked to the data collection procedure (see Chapter 10) in so far as that it is performed centrally using the ICW Care Manager as platform.

All eligible patients participating in the study will be registered in the software during a three-month wash-in phase, along with the physician-reported information about eligibility criteria (see Chapters 5 & 6) and type of medical therapy. The ICW Care Manager contains virtual folders for the two groups (PTC vs. TAU) within participating primary care practices.

The randomization authority (a designated person not involved in care of the trial patients and analysis of data) will access the database of registered patients in a weekly interval to monitor the recruitment process. Recruited and registered patients who fulfill the inclusion criteria will be centrally randomized (stratified by type of medical therapy and PCP) to PTC vs. TAU using a computerized random number generator to create randomization lists for each stratum. The allocation will be documented separately in an Excel file with restricted access except for the randomization authority.

Patients' allocation to either intervention or control group will remain concealed until data collection related to primary and secondary outcomes at baseline (To) has been completed. After baseline data collection has been completed, PCPs will be informed about the allocation of "their" patients (identified through their unique study-ID) with an official letter from the intervention coordinating center (GGM), who in turn receives the information from the study coordinating center (AMV).

## 8. Intervention/Study implementation

The intervention is a complex case management intervention (23) aimed at improving diabetes self-care behavior among patients with type 2 diabetes and multiple comorbidities. The development of the multifaceted intervention (Figure 1) is based on:

- (i) experiences of a 12-month pilot study of the GGM (GEDIMA) including 171 patients at baseline
- (ii) focus groups with PCP physicians and specialist care providers involved in diabetes care, and
- (iii) the active engagement of local patient self-help groups in formulating assessment contents and identifying community resources.

Detailed evaluation of the pilot study is still ongoing and will be completed end of October 2013 (pers. communication [name]/GGM). Preliminary results show a high acceptance among patients (N=171 at baseline, N=151 after 12 months, drop-out rate: 11.7%). The feasibility of the HCA-led, PCPnet-based care management intervention has been sufficiently tested among the 30 PCPs participating in the current study.

The complex intervention is delivered as add-on to usual care and consists of 3 main elements:

### **Assessment**

At the beginning, patients in the PTC-group receive an IT-based assessment (see Appendix: Studienhilfsmittel Formulare “Erstkontakt Assessment”/“Folgekontakt Assessment”) of medical and non-medical needs and resources using a structured protocol by a PCP-net based HCA who functions as net-case manager (NCM).

The NCM is authorized to the ICW Care Manager with a unique password and username. At the beginning, the NCM has only access to pseudonymized data of those recruited patients in the intervention arm, which are based at the PCPs for which she is in charge. The NCM contacts the PCPs in order to de-pseudonymize ‘her’ patients and to deliver the assessment.

Contents of the assessment are: demographics (age, sex, insurance status, living environment, education, migration status/cultural background), utilization of existing health and social services related to individual need (participation in DMPs beyond DMP Diabetes, hospitalization in the last 12 months, social services (Sozialdienst), home nursing services (Pflegedienst), medical aids, physiotherapy, podiatrist, psychotherapy, selected symptoms/clinical manifestations (thirst, lack of appetite, nausea, vomiting, dyspnea, fatigue, wounds, disorientation), biomedical parameters (blood pressure, weight, height, blood sugar), SMBG, participation in diabetes education programs, problems in organization of care and social situation, tripping hazards and social resources (external care givers, family, neighborhood).

Additionally, the NCM performs the following standardized, clinical assessments: mini mental status test (MMST), activities of daily living (I-ADL), tandem stand. Depression (WHO5), mobility/physical activity, alcohol use (AUDIT-C) and tobacco use (pack years) are assessed to identify entry points for individual support. The IT-platform provides the NCM with (physician reported) background information related to diagnoses, medication, HbA1c, proteinuria and potentially existing patient decrees (Patientenverfügung, Vorsorgevollmacht, Betreuungsverfügung).

The results of the initial assessment will be reported to a dialogue assistant based at the PCP, who in turn reports to the caring PCP in charge of the patient. The assessment results serve as the basis to set common goals between patient and PCP based on individual need.

Assessment results will be digitally stored by the software on a secured server (see Chapter 15) to inform the NCM during follow-up (FUP) home visits and during the telephone-monitoring. FUP home visits will occur 6 months (FUP1) and 12 months (FUP2) after entry to the study for patients in the PTC-group (Figure 1).

## **Symptom and Needs Monitoring**

NCMs will deliver a regular telephone-monitoring using a structured monitoring list (see Appendix X). Content and frequency of the monitoring are fixed, but additional items may be determined by the PCP and the NCM. The NCM will deliver (at least) a total of 24 telephone-monitoring sessions according to a fixed schedule (2-weekly for a period of 6 months, monthly for the rest of the intervention period for patients in the PCT-group (Figure 1). Monitoring items contain new diagnoses, dyspnea, incidence/frequency/severity of hypoglycemia, blood pressure, weight, fatigue, medical/social problems and follow-ups on previously mentioned problems and hospitalizations since the last contact. The monitoring list (see Appendix: Studienhilfsmittel "Checkliste Telefonmonitoring") has been developed based on experiences of GGM in prior studies (GEDIMA). Item responses include 'red flags' according to the urgency of the symptoms and signs presented by the patient. These responses will guide the NCM-Patient-PCP interaction. 'Red flag' answers require immediate contact to the PCP to discuss and undertake further steps.

## **Digital structured blood glucose testing**

Additionally, digital structured blood sugar testing (using Roche Diagnostics' Accu Chek® Smart Pix Device and ACCU-Chek® 360°) is applied after T1 for symptom monitoring in 3-monthly interval (in total 3 times) (Figure 1). The NCM collects the individual blood sugar profiles, transfers them into the ICW Care Manager and reports the profiles to the PCP in charge of respective patients. The blood sugar profiles serve as basis for the telephone coaching.

## **Composition and training of case management teams**

The care management teams consist of 11 NCMs, 30 PCP physicians and 30 so called dialogue assistants (DA) based at each PCP. Each NCM cares for about 26 patients from about 3 PCPs.

N=3 NCMs have previously participated in care management interventions related to diabetes and CHD (GEDIMA and KHK-ProMA), N=2 have previously participated in care management interventions related to CHD alone (KHK-ProMA), N=6 have no experience with care management programs.

N=1 NCM is a native Turkish-speaker specialized in the provision of diabetes education. This NCM will be responsible to deliver the care management intervention to patients with a Turkish background in case of language barriers or cultural preferences. We thereby aim to address the special needs of this social group, which constitutes about 22% of the population (on December 30, 2012) in the city where the majority of study centers (PCPs) will be based (i.e. Mannheim, Germany). Potential language barriers to data collection will be accounted for by means of a Turkish version of the patient questionnaire.

Prior to the beginning of the intervention, all NCMs will be trained according to a team-based training curriculum. The curriculum was developed based on experiences from the preceding pilot study (GEDIMA) and inputs from representatives of local patient self-help groups. Completion of a 32 hours team-based training course is mandatory for participating HCAs to function as NCM.

## **Control**

In the control group (TAU), practice teams will continue to provide standard care in the context of the PC-centered care contract. This involves gate keeping for enrolled patients as well as regular training in evidence-based guidelines through structured pharmacotherapy feedback in peer review groups [39]. As population-based disease management programs (DMPs) for diabetes and other selected chronic diseases are part of routine care in Germany, patients may voluntarily participate in these disease specific care programs. German DMPs consist of regular follow up visits up to every three months. They include clinical examination, laboratory tests (e.g. HbA1c tests), patient education, and referral to specialists (ophthalmologists, cardiologists, nephrologists, neurologists) on a regular basis and according to acute needs (16). However, essential elements of care management interventions like individualized assessment, care planning including non-medical aspects, home visits, and frequent (symptom) monitoring are not routinely part of DMPs (6).

## **Fidelity to the study protocol and variability between sites and care management teams**

The intervention seeks to ensure fidelity to the study protocol as far as adherence to the elements of the intervention and the timeline (see Figure 1) are concerned. The IT-supported delivery of the intervention allows assessing fidelity to the main intervention elements for all participants in the intervention group. However, the intervention is explicitly designed to allow adaptations to local contexts, individual needs, preferences and cultural backgrounds as far as the consequences of structured assessment and telephone monitoring are concerned. Adaptations to local contexts and individual preferences (e.g. differential use in community resources and services) will be documented in the ICW Care Manager by the NCM during her routine contacts.

Figure 1 illustrates the elements and the timeline of the intervention.

**Figure 1: Graphical illustration of elements of the complex intervention and the study timeline**

[figure not shown]

Adapted from: Perera et al. (2007) (44)

Dept. for General Practice and Health Services Research- University Hospital Heidelberg

„A multi-center, individual-level randomized, 18-month, parallel-group superiority trial to compare the efficacy of a complex primary care practice network-based care management intervention versus usual care in the improvement of self-care behavior among patients with type II diabetes and multiple comorbidities (GEDIMApus)“

Version 1.0 – 29.10.2013

## **9. Recruitment of study centers, patients and patients' caregiving family members**

### **9.1 Study centers**

The multicenter RCT will be conducted in 30 PCPs. PCPs who formerly participated in a pilot study (GEDIMA) of the GGM will be invited by an official letter from the study central office to participate in the study and need to give their written consent for participation.

### **9.2 Patients**

From the study central office (via the intervention coordination center GGM), the 30 PCPs receive a list with inclusion and exclusion criteria for patients (see above) along with a screening list with random numbers. PCPs are asked to create a list of all potentially eligible patients registered in their practice software based on the inclusion and exclusion criteria.

In a next step, PCPs select 40 patients from the list according to the sequence indicated by the random numbers. Randomly selected patients will be contacted and asked for participation in the study by the PCP physician. Patients not willing to participate will be asked to give a reason for their decision (on a voluntary basis). The number of patients screened, asked, asked and not included as well as the reasons for inclusion, exclusion or non-participation will be documented by the PCP physician and reported to the study central office.

The procedure will be repeated until a total of 20 patients per PCP are recruited.

Patients willing to participate will be informed by the PCP physician about aims, content, privacy issues and risks related to the study. Patients giving their consent to participate in the study will undergo clinical examination and will receive the patient questionnaires (see Appendix) which capture the PROs.

### **9.3 Patients' 'caring' family member**

Patients giving their consent to participate in the study will be asked to hand over (on a voluntary basis) an information leaflet, an informed consent form and a questionnaire in a closed-envelope to their family member who 'cares most' for them. The participation of the 'chosen' family member is completely voluntarily, and independent from the participation of the patient who 'chooses' the family member (for details see Chapter 10: Data collection). Data collected from the patients' family member will be pseudonymized in a way that allows linking the informal care burden with the disease severity of respective patients.

## 9.4 Financial incentives

Participating PCPs receive a compensation per recruited patient and completed assessment at baseline (T0: 25,- €), endpoint (T1: 30,- €) and follow-up (T2: 25,- €) respectively (in total 80,- €). DAs receive 20 Euros per patient per PCP for coordination and communication tasks. NCMs enter a minor employment contract with the GGM (on a 400,- Euro basis) in order to ensure compensation for the delivery of the intensive care management intervention. Participating patients and their respective family members receive no compensation.

## 10 Data collection

After obtaining written informed consent, patients will be registered in the study central office of the Department of General Practice and Health Services Research Heidelberg (AMV) which is responsible for administration, coordination, data management and monitoring (includes database-set up and validation, data entry, coding, and query management).

The intervention coordinating center of the “Genossenschaft Gesundheitsprojekt Mannheim e.V.” (GGM) will carry joint responsibility for administration, validation and data entry.

Patients will be asked by the recruiting physician to fill in a pseudonymized paper-based questionnaire and hand them back to the recruiting physician in a closed envelope. This questionnaire (see Appendix: Patientenfragebogen) captures the patient reported outcomes (PROs) analyzed in this study.

PCPs will document additional data from patients’ chart in a pseudonymized paper-based questionnaire (including inclusion/exclusion criteria, diagnoses, medication, and hospitalization/hypoglycemia prior to recruitment) and assess the clinical status of the patient (e.g. blood pressure, blood glucose, latest HbA1c value). The pseudonymized physician questionnaire will not contain any data that allows identification of patients’ identity. The patient questionnaire and physician reported chart-review will be performed at baseline (T0), 9 months (T1), and 18 months (T2) follow-up.

In addition, patients will be asked to hand over the FFB questionnaire (in a closed envelope along with additional background information) to their relative who ‘cares most’ for them regarding their diabetes, in order to capture the cost of informal care for the health economic evaluation. This questionnaire will be pseudonymized in a way that allows a linkage to the study ID of respective patients.

The collected data is directed to the study central office (AMV) via the following channels:

1. Physician reported chart-review and patient questionnaires will be sent by the PCPs in paper-based format to the study coordination center (GGM) via mail. Here, an authorized employee of GGM

Dept. for General Practice and Health Services Research- University Hospital Heidelberg

„A multi-center, individual-level randomized, 18-month, parallel-group superiority trial to compare the efficacy of a complex primary care practice network-based care management intervention versus usual care in the improvement of self-care behavior among patients with type II diabetes and multiple comorbidities (GEDIMApplus)”

Version 1.0 – 29.10.2013

enters the chart-review data into the ICW Care Manager and thereby registers participating patients with their study ID. All data entered into the ICW Manager will be transferred (via internet) to the Center for Information- and Medical Technologies (Zentrum für Informations- und Medizintechnologie, ZIM) and stored on a secured server (see Chapter 15: Ethics and legal aspects). Authorized clinical monitors based at the AMV can access the stored data in 'real time' in order to check conformity with inclusion criteria and in order to monitor the progress of the recruitment process. Validation of entered data occurs via built-in 'checks' by the ICW Care Manager and by clinical monitors.

2. The paper-based patient questionnaires containing the chart reviews and PROs will be stored at the GGM office and picked up by an employee of the study central office (AMV) in regular intervals.

3. The FFB questionnaire designed for patients' relatives will be sent directly to the AMV by patients' relatives using enclosed, postpaid envelopes. The written consent forms for patients' relatives will be sent to the GGM.

Patient questionnaires and FFB questionnaires will be scanned and digitally stored on a secured server of the AMV.

### **10.1 Monitoring**

The following risk adapted strategy will be deployed to ensure adherence to the study protocol as far as data collection and legal/ethical aspects are concerned. Authorized employees of the study central office (AMV) will conduct practice visits at 10% of PCPs randomly selected from the pool of participating PCPs during the first 3 months of the intervention. The monitoring will include:

- (i) an inspection of informed consents and patients existence of all patients recruited by the PCP,
- (ii) a review of patient charts of 10% of patients recruited by these PCP's in order to check conformity among documented items (see Appendix: Arztfragebogen für Ersterhebung) and source data.

A detailed monitoring manual will be developed by the study central office prior to the beginning of the intervention. Depending on the results of these visits, further quality assurance measures will be defined by the study central office (AMV) and the intervention coordinating center (GGM).

## **11 Statistics**

A detailed description of the statistical methods of this study will be provided in a Statistical Analysis Plan (SAP). Data analysis will be done blinded to treatment arm allocation (i.e. the treatments will be identified as 1 and 2 until analysis is complete). The primary analysis will be based on the 9-month follow-up data (T1).

### 11.1 Populations for analysis

The Intention-to-treat (ITT) population will consist of all randomized patients. Following the ITT principle, patients will be analyzed in the treatment arms to which they were originally randomized, regardless of whether they refused or discontinued treatment, or whether other protocol deviations are known.

The Per-protocol (PP) population will consist of those ITT patients with no major protocol violations. The criteria for the exclusion of patients from the PP population will be determined by the study team at the latest before database lock.

### 11.2 Statistical hypotheses, methods and analyses

The primary objective of this study is to determine the effectiveness of a complex intervention compared to usual care. The primary efficacy endpoint is the change in SDSCA-G score from baseline (To) to 9 months after baseline (T1), i.e. the difference SDSCA-G T1–To. The study objective will be statistically formulated as a test of the null hypothesis  $H_0: \mu_1 = \mu_2$  (the mean difference SDSCA-G T1–To is equal in the two groups) against the alternative hypothesis  $H_1: \mu_1 \neq \mu_2$  (the mean differences SDSCA-G T1–To are different in the two groups). The null hypothesis will be tested at the two-sided significance level of  $\alpha=0.05$ .

The primary efficacy analysis will use a multilevel regression approach with patients at level one and NCMs at level two. The primary model will include treatment group as fixed factor, NCMs as random factor with the baseline value of SDSCA-G and type of medical treatment as covariates. The results will be presented as the mean between-group difference in SDSCA-G T1–To with the corresponding 95% confidence interval. The associated Cohen's effect size  $d$  will be calculated. To support the primary analysis, all potentially relevant baseline characteristics will be added as covariates to the model in sensitivity analyses. A further sensitivity analysis of the primary endpoint will include an unadjusted two-sample t-test on change in SDSCA-G from baseline to 9 months after baseline. Results from these sensitivity analyses will serve to explain and interpret the results of the primary analysis.

The primary analysis will be performed adhering to the intention-to-treat principle. An additional sensitivity analysis will be conducted on a per-protocol analysis set.

The statistical analyses of the secondary endpoints numbered 1-6 (see pages 4-5) will use the same multilevel approach as the primary analysis. According to the scaling of the considered endpoint, a linear or logistic two-level regression model will be fitted. The results will be presented in an analogous manner to the primary analysis. All statistical tests will be two-sided at the significance level of  $\alpha=0.05$ .

The equity-efficacy ratio (45) (and respective 95 % confidence intervals) will be calculated as the ratio of effects at T1 on health outcomes (change in SDSCA score; HbA1c%; HRQL) between the highest and the lowest socioeconomic group (related education/income/subjective social status) for both groups (PTC vs. TAU) compared to To. Additional consideration of social group sizes will be ensured by calculating the concentration index (PTC vs TAU) and plotting concentration curves at To and T1 respectively.

Subgroup analysis for nominal social groups will be performed by means of interaction terms for migration status (Turkish migrants, non-Turkish migrants, participants without migration background) to be included in the regression equations for respective health outcomes (change in SDSCA score; HbA1c%; HRQL) at T. If the tests of subgroup interaction effects are significant below the 0.05 level, further analysis will be performed to check whether their effects are independent (46).

Statistical analyses related to secondary outcomes 8 and 9 (see pages 4-5) focus on the incremental cost effectiveness ratio (ICER) (47, 48). The ICER relates cost differential to outcome differential between intervention and control groups. Bootstrap methods model statistical uncertainty and the net-benefit approach is applied (49, 50). Maximum willingness to pay thresholds and cost-acceptability curves (51, 52) will be determined. Sensitivity analyses will provide information on robustness of assumptions.

Because no adjustments for multiple endpoints are planned, findings (especially those related to secondary outcomes and subgroup analyses(46)) will be interpreted with caution in view of the number of statistical tests undertaken. Only the result of the primary efficacy analysis will be interpreted in a confirmatory manner. Confirmatory subgroup analyses are not planned. No interim analysis with regard to efficacy will be done.

In case of missing data, multiple imputation will be used to complete the data set for analysis. A complete-case analysis will be performed to assess the influence of missing data and the value of adopting multiple imputation methods.

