Access control **in** the application is ensure via user administration, which allows definition of roles and permission to restrict functionality (read, write, create, update, delete) on an GUI level and to restrict access to data objects. Patient level security is guaranteed via restriction of visibility of patients and all patient related data to a user or a group of users (e.g. to guarantee that NCMs only have access to digital records of 'their' patients in the intervention am, but not to those of other NCMs or to the control group).

Audit control includes a GUI based audit feature, which allows a user with the relevant permissions (e.g. the authorized clinical monitor) to query an audit log that contains entries of all relevant accesses on the system with specification of accessing user, date, time, type, scope and accessed data object. Furthermore, through technical, file based logging the application itself logs technical information to disk based log files that may contain relevant information such as system startup, shutdown timestamps and import processes.

The study protocol will be submitted to the ethics committee of the Medical Faculty of the University of Heidelberg prior to the start of the study. Neither patients nor their relatives will be recruited before obtaining the committee's approval.

As mandated by the International Committee of Medical Journal Editors (ICMJE), the trial will be registered in a clinical trial registry after obtaining ethical approval.

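### The primary model nests both arms within NCMs, but NCMs treat only PTC patients; a shared NCM intercept largely cancels from the treatment contrast and leaves the standard error too small if NCMs differ

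*Protocol*

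**What the plan says.** Section 11.2 fixes the structure of the only confirmatory analysis: "The primary efficacy analysis will use a multilevel regression approach with patients at level one and NCMs at level two". Treatment group is a fixed factor, with "NCMs as random factor with the baseline value of SDSCA-G and type of medical treatment as covariates". Secondary endpoints 1 to 6 use the same multilevel approach. Section 11.1 defines who enters: "The Intention-to-treat (ITT) population will consist of all randomized patients", analysed as allocated even if they refused or discontinued treatment.

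Sections 8 and 15 describe who the NCMs are and whom they treat:
- Section 8, Composition and training: "The care management teams consist of 11 NCMs, 30 PCP physicians", and "Each NCM cares for about 26 patients from about 3 PCPs".
- Section 8, Assessment: "the NCM has only access to pseudonymized data of those recruited patients in the intervention arm". The same sentence goes on to tie those patients to the practices for which the NCM is responsible.
- Section 15: access rights let NCMs see the records of their own intervention patients, "but not to those of other NCMs or to the control group".
- Section 8, Composition and training, on the Turkish-speaking NCM: "This NCM will be responsible to deliver the care management intervention to patients with a Turkish background", on condition that there are language barriers or cultural preferences.

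Section 3.1 places both arms in each practice. Section 7 stratifies randomization by practice and by type of medical treatment.

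**The concern.** A two-level model with patients inside NCMs suits a trial in which every patient has an NCM. Here only PTC patients do. Nothing in the protocol says which NCM a TAU patient belongs to, or whether the NCM effect may differ between arms.

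The second omission does the damage. A random NCM intercept shared by both arms describes outcomes that are higher or lower for everyone in an NCM's practices. What partial nesting adds is different: some NCMs may deliver a better intervention than others, and this moves PTC patients only. A shared intercept is subtracted out when PTC and TAU are compared within the same NCM, so that second source of variation never reaches the standard error of the treatment effect.

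Such variation is plausible from the protocol itself. Six of the 11 NCMs have no care-management experience, section 8 allows the intervention to be adapted to local context and individual preference, and the choice of NCM as random factor suggests that the authors expected NCMs to differ. At stake is the type I error of the only confirmatory test, and the same weakness in secondary endpoints 1 to 6.

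**Working it through.** **1. The plan's own figure.** Section 11.4 gives a difference of 0.5 days, SD 2.0, 80% power and a two-sided 5% t-test. The normal approximation is 2 × (1.96 + 0.8416)² × (2.0/0.5)² = 251.2, so 252 per arm. The exact t-test needs 252.13, so 253 per arm and 506 in total, as stated; 506 × 1.15 = 582, or 291 per arm. No clustering term enters.

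**2. Whom the NCMs treat.** 11 NCMs × about 26 patients = 286, which matches one arm (291). If NCMs covered both arms, the caseload would be 582/11, about 53. The caseload agrees with the access rules: NCMs treat PTC patients only.

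**3. Inputs for the standard error.**
- SD of change 2.0 (section 11.4).
- Patients analysed: 291 × 0.85 = 247 per arm (15% drop-out, section 11.4).
- 11 NCMs (section 8).
- NCM intraclass correlation (ICC) in PTC: not given. Assumed 0.02 and 0.05; 0 in TAU.
- Equal caseloads, no baseline adjustment, normal quantiles.

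**4. Standard error that reflects the design.** Variance = 2.0² × [(1 − ICC)/247 + ICC/11 + 1/247].
- ICC 0.02: 4 × (0.003968 + 0.001818 + 0.004049) = 0.03934; SE 0.198 days.
- ICC 0.05: 4 × (0.003846 + 0.004545 + 0.004049) = 0.04976; SE 0.223 days.

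**5. Standard error from the shared-intercept model.** TAU patients take the NCM of their practice. The intercept drops out of the contrast, leaving approximately 2.0 × √[(2/247) × (1 − ICC/2)].
- ICC 0.02: 0.179 days.
- ICC 0.05: 0.178 days.

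**6. Type I error.** 2 × [1 − Φ(1.96 × SE from step 5 / SE from step 4)].

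| ICC (assumed) | SE, shared intercept | SE, partially nested | Two-sided type I error |
|---|---|---|---|
| 0 | 0.180 | 0.180 | 5.0% |
| 0.02 | 0.179 | 0.198 | 7.7% |
| 0.05 | 0.178 | 0.223 | 11.8% |

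The approximation in step 5 matters little. Using the plain unclustered SE, 2.0 × √(2/247) = 0.180, the ratios give 1.96 × 0.1800/0.1983 = 1.778 and 1.96 × 0.1800/0.2231 = 1.581, that is 7.5% and 11.4%.

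Two sets of 400 simulated trials per ICC gave 7.3% and 8.5% at ICC 0.02, and 11.3% and 10.3% at ICC 0.05. Each has a Monte Carlo standard error of roughly 1.3 to 1.6 points, so they are consistent with the formula, but at ICC 0.02 they are weak evidence by themselves.

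**7. Power under the partially nested model, 253 per arm.** The formula of step 4 with 253 in place of 247 gives SE 0.196 (ICC 0.02) and 0.221 (ICC 0.05). Power for 0.5 days is Φ(0.5/SE − 1.96): 72% and 62%, against the planned 80%.

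**The case against.** The strongest reply is that the model can be fitted. NCMs are responsible for practices, about three each, and both arms sit in every practice, so each TAU patient can take the NCM of the practice. This stands. A reader might infer from the missing level-two unit that the primary model is undefined for half the sample and has no valid standard error at all. The protocol does not support that: a usable link exists, though it is unstated. Nor does it suggest leaving the NCM blank in TAU or treating TAU as one large cluster, so those codings should not be used to size the problem. The Turkish-speaking NCM makes the practice link imperfect for some PTC patients; it does not break it, because the reassignment is conditional and every patient has a practice.

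A reader might also infer that an NCM identifier would reveal which coded arm is PTC, against the blinded analysis in section 11. Under the practice link the identifier exists in both arms and reveals nothing. The model recommended here does need to know which arm is PTC, so this argument counts at least as much against the remedy.

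Two further replies have some force. The ICC is assumed, and at 0 there is no error. Section 11 also leaves detailed methods to a SAP that is not at hand. The first limits what can be said about size. The second does not remove the point, because section 11.2 itself fixes the level-two unit and the random factor, and that structure does not match the design described in sections 8 and 15.

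**Conclusion.** The point holds. Section 11.2 specifies full nesting for a partially nested design. Its most natural implementation runs, but omits variation between NCMs in the delivered effect from the standard error of the primary contrast. If NCMs account for 2 to 5% of the variance of change in PTC, the SE is about 0.18 days where 0.20 to 0.22 is right, and the nominal 5% test has a type I error of about 8 to 12%.

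These figures rest on SD 2.0, 247 analysed per arm, 11 equal NCM caseloads, and an NCM effect in PTC only with an assumed ICC. The structural mismatch does not depend on the ICC; its consequence does, and vanishes at 0. It should be settled before arm labels are attached to the data, since it concerns the only test to be read as confirmatory.

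**What to change.** In section 11.2, replace the common NCM random intercept with an NCM random effect that acts in PTC only, or a random NCM-by-treatment effect. In the same text:
- Define NCM as the NCM assigned at randomization, so that PTC patients who refuse or discontinue keep a level-two unit and stay in the intention-to-treat analysis.
- Use Satterthwaite or Kenward-Roger degrees of freedom, because there are only 11 NCMs.
- Include practice, which is a randomization stratum (section 7) but absent from the model.
- Apply the same structure to secondary endpoints 1 to 6.

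The edit is wording only, but it has costs that should be stated. The interval widens if NCMs differ, and power for 0.5 days with 253 per arm falls from 80% to about 72% at ICC 0.02 and 62% at ICC 0.05. Section 11.4 should acknowledge this. The model also identifies the PTC arm, so the analysis code should be fixed and locked before arm labels are attached.
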